### 10.3.2. Vital signs

- Measuring at every visit.
- Blood pressure, pulse rate, respiratory rate, and body temperature

### 10.3.3. Clinical laboratory examination

- Evaluation following items at Visit 1 (Screening), Visit 3 (Week 4), Visit 4 (Week 8), and Visit 5 (Week 12).

#### 10.3.3.1. Hematology test

- Hemoglobin, Hematocrit, RBC, WBC, WBC differential cell count, Platelet

#### 10.3.3.2. Biochemical test

- Alkaline phosphatase, BUN, Creatinine,  $\gamma$ -GTP, SGPT(ALT), SGOT(AST), Albumin, Protein, Total bilirubin, CRP, LDH, sodium, potassium, chloride, phosphorus, calcium

#### 10.3.3.3. Urinalysis

- pH, specific gravity, Protein, Glucose, Ketones, Bilirubin, Blood, Urobilinogen, Nitrite, WBC

#### 10.3.3.4. Blood clotting test

- PT, aPTT

Version 2.6

#### 10.4. Economic assessment

- Evaluation at Visit 2 (Week 0), Visit 3 (Week 4), Visit 4 (Week 8), and Visit 5 (Week 12).
- The patients' health status will be evaluated using the EQ-5D-5L questionnaire.
- This questionnaire consists of five dimensions (mobility, self-care, usual activities, pain/discomfort, and anxiety/depression), each with five levels (no problems, slight problems, moderate problems, severe problems, and extreme problems; scores of 1 to 5).  
The EQ-5D-5L health states are defined by combining one level from each of the five dimensions, for a total of 3125 possible health states. (from [www.euroqol.org](http://www.euroqol.org))
- It is used as a measure of quality of life for future economic evaluation.

Under each heading, please tick the ONE box that best describes your health TODAY.

##### MOBILITY

- |                                           |                          |
|-------------------------------------------|--------------------------|
| I have no problems in walking about       |  |
| I have slight problems in walking about   |  |
| I have moderate problems in walking about |  |
| I have severe problems in walking about   |  |
| I am unable to walk about                 |  |

##### SELF-CARE

- |                                                     |                          |
|-----------------------------------------------------|--------------------------|
| I have no problems washing or dressing myself       |  |
| I have slight problems washing or dressing myself   |  |
| I have moderate problems washing or dressing myself |  |
| I have severe problems washing or dressing myself   |  |
| I am unable to wash or dress myself                 |  |

##### USUAL ACTIVITIES (e.g. work, study, housework, family or leisure activities)

- |                                                    |                          |
|----------------------------------------------------|--------------------------|
| I have no problems doing my usual activities       |  |
| I have slight problems doing my usual activities   |  |
| I have moderate problems doing my usual activities |  |
| I have severe problems doing my usual activities   |  |
| I am unable to do my usual activities              |  |

##### PAIN / DISCOMFORT

- |                                    |                          |
|------------------------------------|--------------------------|
| I have no pain or discomfort       |  |
| I have slight pain or discomfort   |  |
| I have moderate pain or discomfort |  |
| I have severe pain or discomfort   |  |
| I have extreme pain or discomfort  |  |

##### ANXIETY / DEPRESSION

- |                                      |                          |
|--------------------------------------|--------------------------|
| I am not anxious or depressed        |  |
| I am slightly anxious or depressed   |  |
| I am moderately anxious or depressed |  |
| I am severely anxious or depressed   |  |
| I am extremely anxious or depressed  |  |

#### 10.5. Medication compliance assessment

Version 2.6

- Adherence will be ascertained at each visit by history taking and counting the returned unused tablets and empty packaging.
- Medication compliance (%) will be evaluated by dividing the actually consumed tablets by the total numbers of tablets prescribed.

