**9.3. Dosage and administration of the trial drugs**

Version 2.6

|                    |                                 | Dosage                                  | Administration                                              | periods  |
|--------------------|---------------------------------|-----------------------------------------|-------------------------------------------------------------|----------|
| Experimental group | Pilogen tab                     | half table (2.5 mg)
four times a day | Four times a day
(after each meal and
before bedtime) | 12 weeks |
|                    | Baekhogainsam-tang Ext. Granule | One packet (4 g)
three times a day   | Three times a day
(before each meal)                     | 12 weeks |
| Control group      | Pilogen tab                     | one tablet (5 mg)
four times a day   | Four times a day
(after each meal and
before bedtime) | 12 weeks |

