## Version 2.6

- 1) No written informed consent obtained
  - 2) Violation of inclusion and exclusion criteria
  - 3) If a prohibited drug is administered during the clinical trial period
  - 4) If the main examination at the start and end of the clinical trial is missing
  - 5) If the clinical trial drug's compliance is less than 70%
- Medication compliance (%) is defined by dividing the actually consumed tablets by the total numbers of tablets prescribed during the clinical trial period, and if this value is less than 70%, it is withdrawn.
  - Other minor violations of the clinical trial plan that are not considered to affect the interpretation of research results are included in the per-protocol analysis by clearly stating the degree and reason for the violation or delay, and comprehensively considering whether the violation or delay affected the clinical trial.

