##### **13.1.3. Efficacy outcomes**

- Efficacy outcomes will be analyzed for both the per-protocol (PP) and ITT populations. In case of discrepancies between the efficacy outcomes of PP and ITT populations, both set of results will be presented and compared, with the PP population considered the main

Version 2.6

analysis and the ITT population as supplementary analysis.

- The ITT population consists of participants who received at least one dose of the clinical trial drugs and underwent efficacy evaluation more than once during the treatment period. In cases of missing values due to dropouts or discontinuation before the clinical trial ends, missing data from dropout participants will be imputed using the last observation carried forward analysis.
- The PP population is a subset of the ITT population. It includes participants who consumed >70% of the prescribed doses of clinical study drugs and completed follow-up visits and corresponding outcome measurements (weeks 4, 8, and 12) during the 12-weeks treatment periods. Participants falling under a 'significant violation of clinical trial plan' will be excluded from the PP population.

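### Compliance is defined by tablets only in sections 10.5 and 12.3, which ignores the granule and contradicts the two-drug per-protocol criterion in section 13.1.3

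*Protocol*

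**What the plan says.** Section 9.3 gives the experimental arm two products for 12 weeks: pilocarpine as half tablets four times a day, and "Baekhogainsam-tang Ext. Granule", one packet three times a day. The control arm takes pilocarpine tablets only. Section 5.1.2 confirms that the second product is a granule.

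The compliance formula appears twice. Section 10.5: "Medication compliance (%) will be evaluated by dividing the actually consumed tablets by the total numbers of tablets prescribed". Section 12.3: "Medication compliance (%) is defined by dividing the actually consumed tablets by the total numbers of tablets prescribed during the clinical trial period". Section 12.3 also lists, among serious violations, "If the clinical trial drug's compliance is less than 70" per cent.

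On data collection, section 10.5 says: "Adherence will be ascertained at each visit by history taking and counting the returned unused tablets and empty packaging". Section 9.9.2 adds a compliance assessment and the return of unused trial drugs at each visit.

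Section 13.1.3, repeated in the protocol summary, defines the PP set: "It includes participants who consumed >70% of the prescribed doses of clinical study drugs". It also requires completed follow-up visits and measurements, and it removes participants with a significant violation of the plan. Efficacy is analysed in both PP and ITT. If the two disagree, both are presented, PP is the main analysis and ITT is supplementary.

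**The concern.** The granule is what separates the experimental regimen from half-dose pilocarpine alone. Section 4.5 reports that the half dose was significantly less effective than the commercial dose in an earlier trial, so the question under test is whether adding the granule makes up the difference. The only compliance figure the protocol defines covers the control regimen completely and omits one of the two experimental products.

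A percentage that cannot register the granule feeds the violation list, while the PP definition is worded for the study drugs in the plural. The same participant can be compliant under one section and ineligible under another. The trial is open-label, so whoever settles PP membership may know the arm, and two conflicting rules leave room for choice. What is at stake is whether the experimental PP group consists of people who took the combination.

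**Working it through.** The protocol states no compliance figure that can be reproduced apart from the 70% limit. The check is to score one participant under each rule.

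**Inputs** (section 9.3; 12 weeks = 84 days)
- Pilocarpine, experimental arm: 4 × 84 = 336 half-tablet doses = 168 tablets.
- Baekhogainsam-Tang: 3 × 84 = 252 packets.
- All doses: 336 + 252 = 588. Whole tablets plus packets: 168 + 252 = 420.

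The ratios do not depend on the number of days: per day the granule is 3 of 7 administrations (42.9%) and pilocarpine 4 of 7 (57.1%).

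**Step 1. Every half tablet taken, no packet taken**

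| Rule | Calculation | Result | Consequence |
|---|---|---|---|
| 10.5 and 12.3, tablets only | 168/168 | 100% | no violation |
| 13.1.3, doses of both products pooled | 336/588 | 57.1% | not in PP |
| 13.1.3, whole tablets and packets pooled | 168/420 | 40.0% | not in PP |
| 13.1.3, granule on its own | 0/252 | 0% | not in PP |

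The tablets-only rule and every two-drug reading of 13.1.3 give opposite answers.

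**Step 2. How few packets a pooled reading of 13.1.3 would accept**

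With full pilocarpine, more than 0.70 × 588 = 411.6 doses are needed, so 411.6 − 336 = 75.6, that is 76 packets. Check: (336 + 76)/588 = 412/588 = 70.1%, with 76/252 = 30.2% of the granule taken. If the limit applied to each product, more than 0.70 × 252 = 176.4 packets would be needed, that is 177.

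**Step 3. The inequality**

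Section 13.1.3 needs more than 70%; section 12.3 calls less than 70% a violation. Exactly 70% is no violation but fails PP. At the full 84-day prescription the thresholds are 235.2 of 336, 176.4 of 252 and 411.6 of 588, so no whole number of doses lands exactly on 70%. This is a minor wording mismatch.

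**Step 4. Direction, as an illustration only**

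The plan's sample size (section 8.4) reproduces: 2 × 0.35² × (1.645 + 1.282)² / 0.21² = 47.6, rounded up to 48 per arm; 48/0.8 = 60. The standard error at 48 per arm is 0.35 × √(2/48) = 0.0714, and power is Φ(0.21/0.0714 − 1.645) = 90%.

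The documents give neither the granule's effect nor the share of non-takers. Assume an effect of 0.05 to 0.21 mL/min and 10% to 30% non-takers kept in PP. The experimental mean then falls by 0.05 × 0.10 = 0.005 to 0.21 × 0.30 = 0.063 mL/min. Power becomes Φ(0.205/0.0714 − 1.645) = 89% down to Φ(0.147/0.0714 − 1.645) = 66%.

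**The case against.** A reader might infer that a participant who takes no granule enters PP and is analysed as having received the combination. The documents do not support that. Section 13.1.3 sets its own dose criterion, worded for the study drugs and not tied to the formula in 10.5. It applies in addition to the violation rule, so passing the tablets-only check admits nobody who fails it. Under any two-drug reading this person is out. A reader might also take PP as the deciding set in every case; it ranks as main only when PP and ITT disagree. Nor does the defect make a false claim of non-inferiority easier if the granule works, since non-takers then lower the experimental mean.

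Other points on that side have some weight. Empty packaging is counted and unused drug is returned, so packet intake can probably be established. The word tablets may be loose shorthand for dose units, though nothing in the text says so. No rate of granule non-adherence is given, and the worked participant is an extreme case. A pooled rule would be a legitimate choice if it were stated.

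What remains is that the protocol fixes a formula, twice, that has no value for one of the two products and disagrees with its own PP wording. This is not detail left to an analysis plan. Section 13.1.3 supplies no calculation of its own, and its pooled reading would still admit someone who took under a third of the packets.

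**Conclusion.** The point holds as a contradiction between sections 10.5 and 12.3 on one side and 13.1.3 on the other. A participant on half tablets alone scores 100% by the stated formula, but 57.1% of pooled doses and 0% of the granule under the PP criterion. Experimental PP membership turns on which text is used and, within 13.1.3, on whether doses are pooled: 76 packets suffice if pooled, 177 if each product counts separately. The control arm is not affected, as it takes tablets only.

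The consequence is chiefly for interpretation: a PP set that includes people who took little or no granule cannot have its result credited to the combination. The loss of power is real only if the granule works, and its size rests on assumed figures. The conclusion takes the prescribed schedule as 84 days, which does not alter the ratios, and takes the serious violations of 12.3 to be the significant violations named in 13.1.3.

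**What to change.** - In 10.5 and 12.3, define two compliance figures: pilocarpine as tablet units taken over tablet units prescribed, and Baekhogainsam-Tang as packets taken over packets prescribed. Say that the packet count comes from the empty packaging and returned unused drug.
- In 13.1.3 and the protocol summary, state that the existing 70% limit applies to each product assigned to the arm, so that PP represents the combination under test. Refer to the figures in 10.5.
- Use the same inequality in 12.3 and 13.1.3, and the same term for the violations that exclude from PP.

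The cost is protocol wording and a packet count from packaging the sites already handle. The downside is that some more experimental participants may leave PP, with none leaving the control arm for this reason. The number excluded for the granule alone should be reported.

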## 11. Predictive side effects and precautions

### 11.1. Pilogen

#### 11.1.1. Predictive side effects

(1) Patients with head and neck cancer

- ① Sometimes the following adverse reactions may occur
  - Sweating, nausea, rhinitis, diarrhea, coldness, flushing, frequent urination, dizziness, helplessness, headache, indigestion, swelling, abdominal pain, amblyopia, vomiting, pharyngitis, hypertension, visual abnormalities, conjunctivitis, dysphagia, ulcer, muscle pain, itchy sense, rash, sinusitis, tachycardia, palpitations, and voice changes
- ② In rare cases, the following adverse reactions may occur.
  - Whole body: Body odor, hypothermia, mucosal abnormalities
  - Cardiovascular system: bradycardia, ECG abnormality, cardiac hypertension, fainting
  - Digestive system: loss of appetite, increased appetite, esophagitis, gastrointestinal disturbance, tongue disease
  - Hematopoietic system: leukopenia, lymph node disease
  - Nervous system: anxiety, confusion, depression, hypermotility, tardiness, nervousness, sensory abnormalities, speech disorders
  - Respiratory system: sputum increase, wheezing, yawning
  - Skin: seborrheic
  - Special sensations: hearing loss, eye pain, glaucoma

## Version 2.6

- Urogenital system: Urology disorder, uterine bleeding, urinary tract disorder
- ③ In long-term treatment, two patients with underlying cardiovascular disease experienced myocardial infarction and fainting, respectively. The causal relationship with the drug is unclear.

## (2) Patients with Sjogren's syndrome

- ① Among the adverse reactions associated with this drug in two placebo-controlled trials, the most frequent were sweating, frequent urination, coldness, and vasodilation (redness), and the most frequent reason why patients discontinued treatment was sweating.
- Sometimes the following adverse reactions may occur
  - sweating, frequent urination, nausea, flushing, rhinitis, diarrhea, chills, increased saliva secretion, helplessness, headache, epidemic cold, indigestion, dizziness, pain, sinusitis, abdominal pain, pharyngitis, rash, infection, accidental trauma, allergic reaction, stomachache, visual field shaking, constipation, cough increase, swelling, facial edema, fever, fart, tongue inflammation, muscle pain, heart palpitations, itching sense, drowsiness, gastritis, tachycardia, tinnitus, incontinence, urinary tract infection, vaginitis, and vomiting
- ② In rare cases, the following adverse reactions may occur.
  - Whole body: chest pain, cyst, death, candidiasis, neck pain, neck stiffness, photosensitivity reaction
  - Cardiovascular system: angina, arrhythmia, ECG abnormalities, low blood pressure, high blood pressure, intracranial bleeding, migraine, myocardial infarction
  - Digestive system: loss of appetite, bilirubinemia, cholelithiasis, colitis, dry mouth, trim, gastritis, gastroenteritis, gastrointestinal abnormalities, gingivitis, hepatitis, liver function test abnormalities, hemoptysis, nausea and vomiting, pancreatitis, dysplasia, salivary gland hyperplasia, sputum increase, loss of taste, tongue abnormalities, tooth abnormalities

## Version 2.6

- Hematopoietic system: hematuria, lymph node disorders, platelet abnormalities, thrombocytopenia, thrombosis, leukocyte abnormalities
- Metabolism and nutrition: Peripheral edema, hypoglycemia
- Skeletal muscle system: joint pain, arthritis, bone abnormalities, natural fractures, pathological fractures, tendon disease, tooth disease
- Nervous system: aphasia, confusion, depression, abnormal dreams, emotional anxiety, hypermotility, tardiness, insomnia, leg cramps, nervousness, dysphoria, abnormal thinking
- Respiratory system: bronchitis, shortness of breath, hiccups, laryngeal spasms, laryngeal inflammation, pneumonia, viral infection
- Skin: alopecia, contact dermatitis, dry skin, eczema, nodular erythema, deprivation dermatitis, herpes simplex, skin ulcers, alveolar rash
- Special senses: cataract, conjunctivitis, dry eye, ear disease, otalgia, ocular disease, eye bleeding, glaucoma, urticaria, retinal disease, taste loss, visual abnormality
- Urogenital system: Breast pain, dysuria, mastitis, excessive menstruation, uterine bleeding, ovarian disease, pyuria, urethral pain, frequent urination, vaginal bleeding, candidiasis

**11.1.2. Precautions****11.1.2.1. Warnings**

- 1) Patients with severe cardiovascular disease: We could not correct the abnormalities of blood flow or beat caused by this drug. When administering this drug to patients with cardiovascular disease, it should be carefully administered under the strict supervision of the doctor.
- 2) Eye: In patients who applied this drug to the eye, especially at night, patients who had vision correction occurred impaired vision, and it has been reported to cause serious perception disorders. Care should be taken when driving at night or doing something

Version 2.6

dangerous in a dark place.

- 3) It has been reported that this drug increases airway resistance, tension in the smooth muscle of the bronchi, and bronchial secretion. When administering this drug to patients with asthma, chronic bronchitis, or chronic obstructive pulmonary disease, it should be administered carefully under the strict supervision of a doctor.

#### **11.1.2.2. Patients contraindicated to administration**

- 1) Asthma patients
- 2) Patients with pilocarpine hypersensitivity
- 3) Ophthalmic diseases (such as narrow angle glaucoma, peripheral retinopathy, and iritis)

#### **11.1.2.3. General attention**

- ① Care should be taken when administering this drug to patients with cholelithiasis or suspected cholelithiasis, or patients with biliary tract disease. Atrophy of the gallbladder or bile duct smooth muscle can promote complications including cholecystitis, cholangitis, and biliary obstruction.
- ② This drug can increase the tension of the ureter's smooth muscle, and theoretically, it can promote renal colic (or ureter's reflux), especially in patients with kidney or ureter stones.
- ③ Choline efficacy drugs have a central nervous system effect in terms of dose. This should be considered in the treatment of patients with psychiatric disorders.
- ④ Patients should be informed that administration of this drug can cause visual impairment, especially at night, to the extent that it is impossible to drive safely.
- ⑤ Dehydration can occur if excessive sweating occurs in the patient when sufficient water cannot be consumed while taking this drug.

## Version 2.6

- ⑥ The drug's toxicity is characterized by an excess of parasympathetic nervous system-like effects. These include headache, visual field disorder, tears, sweating, dyspnea, gastrointestinal dystrophy, nausea, vomiting, diarrhea, atrioventricular block, tachycardia, bradycardia, hypotension, hypertension, shock, delirium, arrhythmia, and progression.
- Cardiovascular pharmacological actions associated with the dose of this drug include hypotension, hypertension, bradycardia, and tachycardia.
- ⑦ Based on the decreased blood clearance rate in patients with moderate liver disorder, the initial dose in these patients is 5 mg twice a day, and adjusted according to the treatment response and tolerability.
- Patients with mild liver disorder (Child-Pugh score 5-6) do not need dose reduction. No pharmacokinetic studies were conducted in patients with severe liver disorder (Child-Pugh score 10-15). The use of this drug is not recommended in these patients.

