## 5. The clinical trial drug information

### 5.1. Overview of clinical trial drugs

#### 5.1.1. Pilocarpine

|                               |                                                                                                                                                                                                                          |
|-------------------------------|--------------------------------------------------------------------------------------------------------------------------------------------------------------------------------------------------------------------------|
| Product name                  | Pilogen Tab.                                                                                                                                                                                                             |
| Manufacturer                  | CTC Bio, Inc.
(Seoul, Republic of Korea)                                                                                                                                                                              |
| Approval date                 | 2008-Jun-18                                                                                                                                                                                                              |
| Formulation                   | white circular film coating tablet                                                                                                                                                                                       |
| Components /
Amounts       | Pilocarpine Hydrochloride 5 mg                                                                                                                                                                                           |
| Authorized
efficacy effect | The treatment of symptoms of dry mouth from salivary gland dysfunction caused by radiotherapy for head and neck cancer.

The treatment of symptoms of dry mouth or dry eye in patients with Sjogren's syndrome.    |
| Dosage &
Administration    | Experimental group: half table (2.5 mg) four times a day, taken orally for 12 weeks

Control group: one tablet (5 mg) four times a day, taken orally for 12 weeks (four times: after each meal and before bedtime) |

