**8.2. Exclusion criteria**

- Patients with the following past medical history
  - heart failure
  - medication-refractory hypertension (systolic blood pressure  $\geq$  160 mmHg or diastolic blood pressure  $\geq$  100 mmHg)
  - bronchial asthma
  - arrhythmia accompanied by clinical symptoms (fainting, palpitation, or shortness of breath) or requiring treatments (sinus failure, atrial conduction block, atrial fibrillation, atrial junction dependent tachycardia, ventricular tachycardia)
  - coronary artery disease
  - asthma, chronic obstructive pulmonary diseases, chronic bronchitis
  - inborn errors of amino acid metabolism
  - hepatic encephalopathy
  - ophthalmic diseases (such as narrow angle glaucoma, peripheral retinopathy, and iritis)
- Clinical laboratory test results falling within the following ranges (within 7 days prior to the start of clinical trial drug administration)
  - hemoglobin  $<$  8.0 g/dL
  - aspartate transaminase (AST) or alanine transaminase (ALT)  $>$  3 times the upper limit of each hospital standard
  - total bilirubin  $>$  2 times the upper limit of each hospital standard

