## Version 2.6

- creatinine >1.5 times the upper limit of each hospital standard, or creatinine clearance  $\leq$  60 mL/min
- Patients taking following medications are also excluded: coumadin, heparin, warfarin, aspirin, anticholinergics, first-generation antihistamines, antidepressants with anticholinergic effects, monoamine oxidase inhibitors, diuretics, mineralocorticoids,  $\beta$ -adrenaline antagonist, or digitalis; patients taking low-dose aspirin or  $\beta$ -adrenaline antagonist can participate in the protocol based on the cardiologist's opinion.
- pregnancy or lactation, disagreement with proper contraception
- Failure to use appropriate contraception methods (male participants), participants who did not agree to contraception for 4 weeks after the end of administration of the trial drug (both male and female)
- galactose intolerance, Lapp lactase deficiency, or glucose-galactose malabsorption
- difficulty in oral administration of a clinical trial drug
- significant hypersensitivity to Baekhogainsam-Tang or components
- significant hypersensitivity to pilocarpine
- Participants who is deemed unsuitable for participation in clinical trials at the discretion of the investigator due to various reasons including screening test results
- cognitive disorder; inability to read and write

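### The fixed 20 mg/day control dose conflicts with the protocol's own hepatic dosing advice, and no eligibility criterion keeps moderate or severe liver disorder out

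*Protocol*

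**What the plan says.** **Dose.** Section 5.1.1 states: "Control group: one tablet (5 mg) four times a day, taken orally for 12 weeks". Section 9.3 repeats this, and gives the experimental arm half a tablet (2.5 mg) four times a day. Neither section has a titration step, a reduced starting dose or a hepatic rule.

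**Hepatic advice.** Section 11.1.2.3, item 7, grades its advice by liver function:
- Mild: "Patients with mild liver disorder (Child-Pugh score 5-6) do not need dose reduction".
- Moderate: because clearance is decreased, "the initial dose in these patients is 5 mg twice a day, and adjusted according to the treatment response and tolerability".
- Severe (Child-Pugh 10-15), where no pharmacokinetic studies were done: "The use of this drug is not recommended in these patients".

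**Eligibility.** Section 8.2 and the matching summary list address the liver through a history of "hepatic encephalopathy", AST or ALT above 3 times the upper limit, and total bilirubin above 2 times the upper limit. Three further provisions could catch some patients:
- 8.2 excludes anyone "deemed unsuitable for participation in clinical trials at the discretion of the investigator due to various reasons including screening test results".
- The excluded medicines include "monoamine oxidase inhibitors, diuretics, mineralocorticoids".
- 9.9.1 tells sites to exclude clinically significant abnormalities found at screening.

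Child-Pugh is mentioned only in 11.1.2.3. It does not appear in the exclusions or in the withdrawal criteria of 12.1.

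**The concern.** A fixed-dose protocol should not admit patients for whom its own text gives a different starting dose or advises against the drug. Here it can. A site that admits a patient with moderate liver disorder into the control arm has no course consistent with both sections: following 9.3 doubles the starting dose in 11.1.2.3, and following 11.1.2.3 departs from 9.3.

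The stake is patient safety. Section 11.1.2.3 lists atrioventricular block, bradycardia, hypotension and arrhythmia among the drug's toxic effects, and 11.1.4 says its pharmacology after oral use in liver disease is unknown. The first scheduled visit and laboratory check after dosing starts is at week 4 (9.9.2, 10.3.3).

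**Working it through.** **1. Daily dose against the protocol's own advice**

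| | Tablets and frequency | mg/day | Ratio to 10 mg/day |
|---|---|---|---|
| Stated initial dose, moderate disorder (11.1.2.3) | 5 mg × 2 | 10 | 1.0 |
| Control (9.3) | 5 mg × 4 | 20 | 2.0 |
| Experimental (9.3) | 2.5 mg × 4 | 10 | 1.0 |

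In moderate disorder the conflict lies in the control arm only. In severe disorder it lies in both arms, since both take pilocarpine.

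**2. Time to the first planned review**

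Visit 3 is at 4 weeks ± 2 days, so 28 ± 2 = 26 to 30 days. Over that time control takes 20 × 26 = 520 mg to 20 × 30 = 600 mg, against 260 to 300 mg at the stated initial dose: an excess of 260 to 300 mg if nothing is adjusted. The duration is the useful figure. Section 4.5 describes a half-life within 3 hours and no cumulative effect, so the summed milligrams are not a measure of harm.

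**3. Do the existing exclusions close the gap?**

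The bands in 11.1.2.3 are mild 5-6 and severe 10-15, which leaves 7-9 for moderate. The protocol does not list the components of the score. Assume the standard five (bilirubin, albumin, clotting, ascites, encephalopathy), each scored 1 to 3. This fits the range from 5 × 1 = 5 to 5 × 3 = 15.

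Take the assumption most favourable to the protocol: anyone who passes 8.2 scores 1 for bilirubin and 1 for encephalopathy. The other three items are free.

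- Lowest possible score: 1 + 1 + 3 × 1 = 5.
- Highest possible score: 1 + 1 + 3 × 3 = 11.
- Albumin 3, clotting 3, no ascites: 1 + 1 + 3 + 3 + 1 = 9, moderate.
- The same with slight untreated ascites: 1 + 1 + 3 + 3 + 2 = 10, severe.

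The numeric limits therefore leave the whole moderate band open and part of the severe band (10-11). The diuretic ban removes patients whose ascites is treated with a diuretic. Without ascites the highest score is 1 + 1 + 3 + 3 + 1 = 9, so on this assumption a severe case needs ascites not treated with a diuretic.

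**4. What follows if a site obeys section 11 instead**

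Two tablets a day in place of four is 2/4 = 50% of the 9.3 dose. Sections 10.5 and 12.3 define compliance as tablets consumed over tablets prescribed. If the denominator is the 9.3 schedule, 50% is below 70%, which is a serious violation and removes the patient from the per-protocol set, the main analysis when the two sets disagree (13.1.3). If the reduced prescription is the denominator, the patient can stay in. Either way that control patient takes 10 mg/day, the same daily pilocarpine dose as the experimental arm.

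**The case against.** The best defence is that item 7 is a general caution and not a trial dosing rule. Section 11.1.2.2 lists the contraindications separately (asthma, hypersensitivity, eye disease), all three are carried into 8.2, and liver disorder is not among them. On this reading the authors turned contraindications into exclusions and left cautions to the clinician. The liver is also screened in several ways: the numeric limits, the diuretic ban, the instruction in 9.9.1, albumin, PT and hepatitis serology at screening, and investigator discretion. Section 15.4 provides for unscheduled visits when adverse events occur. The worked scores above depend on components that the protocol does not give.

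Part of this stands. The number exposed is probably very small, no effect on sample size or the primary method follows, and the cumulative dose adds little.

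The rest does not remove the gap. The authors did not stop at contraindications: chronic bronchitis and chronic obstructive pulmonary disease (a warning in 11.1.2.1) and β-antagonists (an interaction in 11.1.2.4) also became exclusions, the latter with an exception on a cardiologist's opinion. Item 7 also differs from its neighbours in 11.1.2.3, because it alone gives a different starting dose and advises against use. The discretionary filters set no hepatic threshold, so four sites can decide differently. Unscheduled visits respond to harm after it has begun. Whatever the score's components, no limit on it is written.

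**Conclusion.** The point holds. Control is fixed at 20 mg/day, which is 2.0 times the starting dose that section 11.1.2.3 gives for moderate liver disorder. The drug is advised against in severe disorder in both arms, and no criterion sets a limit on the Child-Pugh score. An affected control patient could stay on the higher dose for 26 to 30 days before the first planned review.

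The dose conflict and the missing limit rest on the protocol text alone. The scores showing which patients could pass 8.2 rest on the assumed standard components. The number of patients affected is not given and may be zero. This is a change the sponsor should make for safety and consistency; it is no threat to the trial's primary conclusion.

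**What to change.** Add to 8.2 and the matching summary list: moderate or severe liver disorder, Child-Pugh score 7 or more. Score it at screening, before allocation, so that it applies equally to both arms. Albumin and total bilirubin (10.1.4.2) and PT (10.1.4.5) are already collected; ascites and encephalopathy need clinical assessment.

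The doses in 9.3 can then stay as written. The alternative, a reduced control dose for moderate disorder, is less attractive because it would give those patients the experimental arm's daily pilocarpine dose and blur the comparison.

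Cost: one line in two places, one extra screening field, and few or no patients lost.
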